### Outcome Variables and Measurements

The primary end point is survival, calculated from the date of entry in the database until death or until 5 years of follow-up are reached. For patients in cohort 1, the earliest date of cancer diagnosis for which they have been selected to be part of the cohort will be considered the date of entry into the study (inclusion criterion).

As study variables, the following data will be collected from all patients:

List of diagnosed diseases (data source: CMBD and ICS ECAP diagnostic registry)Date of death (data source: INE cause of death registry)Cause of death (data source: INE cause of death registry)Pharmacological treatment (data source: Catalan electronic prescription), including all prescribed active ingredients, drug withdrawal dates from pharmacies, consumed doses, and prescribed regimen, during the entire follow-up periodSex (data source: Sistema Integral d'Informació de Salut)Date of birth (data source: Sistema Integral d'Informació de Salut)Basic health area (data source: Sistema Integral d'Informació de Salut)

For the patients included in the study with one of the cancers under study (cohort 1), the following variables will also be collected:

Type of cancer and presence of metastases (data source: CMBD and ICS ECAP diagnostic registry)Date of diagnosis for which the patient is included in the cohort (data source: CMBD and ICS ECAP diagnosis registry)Surgical treatment of the cancer (data source: CMBD)Date of surgical treatment (data source: CMBD)

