### Machine Learning

Machine learning techniques can reveal associations between variables, which are difficult to discover through statistical analyses [18]. Given the large volume of active ingredients to be analyzed and the high number of cases included in the database, in this study, as an additional step to the statistical analyses described below, machine learning techniques will be used to identify associations between the consumption of drugs and survival. The associations identified by machine learning techniques will later be confirmed by the classical statistical analyses described below.

Association rule mining (ARM), widely used for medical data analysis, will be used [19-21]. Through this method, association rules (ARs) are constructed that represent possible relationships between different elements within large data sets, identifying the most relevant ones. ARs consist of an antecedent (left hand side), which can be made up of several elements (drugs, age, etc), and a consequent (right hand side), which is made up of a single element, in the case of this study, survival at 5 years. In this study, a total of 2 sets of different ARs will be built using two approaches: (1) based on the amount of drug consumed, and (2) based on the time of drug consumption.

All variables will be previously categorized for use by the ARM technique. The survival variable will be treated dichotomously, depending on whether the patient has survived for at least 5 years. To obtain the set of rules based on the time of consumption of the drugs (active principles [ATC4] and families [ATC5]), the information will be categorically organized by quarters: whether the drug has been consumed during the quarter or not. To construct the set of rules related to the doses of drug consumed, the average DDD, discretized in 3 quantiles, will be used during the survival time of the patient.

Among all the rules generated by this methodology, the relevant ones will be selected. For this, an a priori algorithm [22] will be used to extract element frequencies, as it has been shown to be effective and is widely used in the literature [23].

Of all the rules produced using this methodology, only those that are met in at least 5 patients will be taken into consideration, and the most relevant will be selected using the following set of metrics:

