As a secondary objective, we plan to analyze the relationship between the presence of various nonneoplastic diseases and the survival of patients with cancer. To do this, we will compare the survival of patients with a specific disease to those who do not have it, adjusting multivariate models for age, gender, other conditions that may impact survival, and medications that have previously been shown to modify survival in previous analyses.

All analyses conducted in the cohort of patients with cancer will be replicated in a control patient group matched by age to the patients with cancer (with expected lower mortality) and in another group of older patients, where each control will be 10 years older than their cancer counterpart (with expected higher mortality). The findings that are reproduced in these groups of the control cohort will be discarded, as they are considered the result of uncontrolled biases or general effects on survival, not related to the cancers under study.

To consider a result statistically significant, the P value will be set at P=.05. All analyses are considered exploratory and hence subject to confirmation in new studies; therefore, no correction techniques will be applied to the P values obtained. All statistical analyses will be performed using R statistical software (version 4.1.0 or higher; R Core Team).

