Finally, such a broad exploration of variables and results will lead to the discovery of many random results due to biological variability that may not be able to be replicated in future research. The researchers will consider the implementation of adjustments such as the “false discovery rate.” Notably, the study is exploratory, and the results must be confirmed in subsequent studies designed to test each hypothesis derived from this study.

In conclusion, this will be a pharmaco-epidemiological study with great potential to discover new drugs that influence cancer, but that, by design, will serve only as a preliminary step, guiding subsequent research aimed at the repurposing of active molecules for the treatment of cancer.

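### The control-cohort discard rule does not test whether a drug effect is specific to cancer, and the two statements on multiplicity contradict each other

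*Protocol article*

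**What the plan says.** - **Discard rule (Statistical Analysis).** All cancer analyses are repeated in an age-matched control group and in a group born 10 years earlier. "The findings that are reproduced in these groups of the control cohort will be discarded", on the ground that such findings reflect bias or general effects on survival. The Abstract (Methods) gives the purpose: to establish whether associations are confined to patients with cancer.
- **Threshold (Statistical Analysis).** "To consider a result statistically significant, the P value will be set at P=.05". Because the analyses are exploratory, "no correction techniques will be applied to the P values obtained".
- **Multiplicity (Discussion).** After conceding that many random results will appear: "The researchers will consider the implementation of adjustments such as the" false discovery rate.
- **Rule mining (Machine Learning).** "The associations identified by machine learning techniques will later be confirmed by the classical statistical analyses described below". No hold-out sample is mentioned.
- **Time origin (Outcome Variables and Measurements).** "The primary end point is survival, calculated from the date of entry in the database until death". For cohort 1, entry is the earliest qualifying diagnosis. For controls, the Duration section asks only for some health care contact in 2006-2012; no index date is stated.

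**The concern.** The product of this study is a list of candidate drugs, and the discard rule decides which drugs stay on it as cancer specific. The rule sets one result in cancer beside another in controls. Two separate results do not tell whether the effects differ: a general effect can be missed in controls because few of them die, and a trivial control effect can be declared because the control cohort is very large. The article does not define reproduction by direction, size, P value, or one group versus both. That is more than a detail left to a fuller plan, because a comparison of verdicts does not answer the question of exclusivity however its threshold is set.

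The filter also cannot stand in for multiplicity control, since a chance finding in cancer has no reason to recur in controls. With Methods and Discussion at odds, and with Results saying that analyses have begun, whether to correct could be decided after the results are seen.

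**Working it through.** **1. The plan's own figure.** Sample Size Considerations gives 294 per group for 20% vs 30% survival, alpha 5%, power 80%. The two-sided pooled formula gives [1.96 x sqrt(2 x 0.25 x 0.75) + 0.8416 x sqrt(0.16 + 0.21)]^2 / 0.10^2 = (1.200 + 0.512)^2 / 0.01 = 293.2, so 294. The figure is right, for one uncorrected comparison in the cancer cohort. No figure is given for the control analyses.

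**2. Chance leads.** The Introduction cites more than 2,600 active ingredients in Spain. The number testable is not given; I assume 500-2,600.
- If all are null: 500 x 0.05 = 25; 2,600 x 0.05 = 130 per cancer per analysis.
- A null drug is reproduced by chance in a control group with probability 0.05 (any direction) or 0.025 (same direction). If either group discards, 130 x 0.95^2 = 117 to 130 x 0.975^2 = 124 remain. If both must reproduce, about 130 remain.

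The filter therefore removes about 0.1-10% of chance leads.

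**3. A general effect, with each cancer compared with its own matched controls.** Power = Phi(sqrt(d x 0.1 x 0.9) x |ln HR| - 1.96), with d deaths and 10% exposed (assumed). Reproduced is read as P<.05.
- Pancreas cases (Table 2): 1,168 a year x 7 years = 8,176. At 8.2% survival, d = 8,176 x 0.918 = 7,506. For HR 0.85, sqrt(675.5) x 0.1625 - 1.96 = 2.26: power 99%.
- Same-age controls: 2 x 8,176 = 16,352. At an assumed 10% mortality, d = 1,635: sqrt(147.2) x 0.1625 - 1.96 = 0.01: power 50%.
- Older controls: also 16,352, mortality assumed.

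| Older-group mortality | Power, older group | Passes if either group discards | Passes if both must reproduce |
|---|---|---|---|
| 15% | 68% | 0.495 x 0.325 = 16% | 1 - 0.505 x 0.675 = 66% |
| 20% | 80% | 10% | 60% |
| 25% | 88% | 6% | 56% |
| 30% | 93% | 4% | 53% |

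The last two columns apply to effects already found in the cases. At 30%, the unstated choice alone changes the answer more than tenfold.

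**4. A second check at the plan's own size.** Take the same odds ratio, (0.30/0.70)/(0.20/0.80) = 1.71, in cancer (294 per group, power about 80%) and in one control group at two controls per case (588 per group). Control power is about 42%, 69% or 92% at assumed control survival of 95%, 90% or 80%. The general effect is significant in cancer and not in that group about 46%, 25% or 7% of the time.

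**5. All same-age controls pooled instead.** 102,860 x 2 = 205,720. At 10% mortality, d = 20,572.
- General HR 0.85: power about 100%, so it is caught.
- Slight HR 0.93: sqrt(1,851.5) x 0.0726 - 1.96 = 1.16: power 88% (60% at 5% mortality, 99% at 20%). A drug with HR 0.70 in cancer could then be dropped.

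**6. What a direct comparison shows.** For cancer HR 0.70 (pancreas) against control HR 0.93 (pooled, 10% mortality), the ratio is 0.70/0.93 = 0.75. SE = sqrt(1/675.5 + 1/1,851.5) = 0.045, giving a 95% CI of 0.69-0.82 and z of about 6.3. The difference that the discard rule could hide is plain. For a truly general effect the expected ratio is 1, and the test's error rate is fixed whatever the number of control deaths.

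**The case against.** Several objections stand in part.

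- **Exploratory status.** The Abstract, Statistical Analysis and Discussion all reserve confirmation for new studies. An uncorrected screen is defensible in that setting. What is not defensible is stating both positions.
- **The older group exists to supply deaths.** It does: if either group discards, leakage falls from about 50% to 4-16%. If both must reproduce, it exceeds 50%. The article does not say which.
- **Reproduced need not mean P<.05.** Correct. A reader might infer that a drug with HR 0.70 in cancer and 0.93 in controls will certainly be thrown out. The text supports only that it could be.
- **The two harms do not occur together.** A reader might infer that the rule both keeps general effects and loses real leads at the sizes above. With pooled controls, general effects are caught; with pancreas-matched controls, HR 0.93 is significant only 14% of the time. Which harm applies depends on the pool used, which is not stated.
- **The filter is not useless.** It does remove general or bias-driven findings when control power is high. Its weakness is with chance leads.
- **A study-wide total of false leads.** Multiplying by nine cancers and two approaches gives 450-2,340. That assumes every drug is null, and it counts the odds-ratio and survival-time analyses of the same patients as separate leads. I do not rely on it.
- **Rule mining.** A reader might infer that the classical step adds nothing. It adds matching and adjustment. It is not independent confirmation, so only the word is wrong.
- **Time origin.** A reader might infer that controls are analysed from a wrong date. The article simply does not state their index date, which a condensed article may leave out.

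**Conclusion.** The point holds in two parts.

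First, the discard rule does not do what the Abstract says the control cohort is for. It estimates no difference in effect, and with reproduction read as P<.05 its answer is set largely by control deaths, by the pool used and by an unstated either/both choice. For a general HR of 0.85 in pancreas cancer, that means 4-16% or 53-66% passing as cancer specific.

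Second, Methods and Discussion contradict each other on correction, and the filter does not fill the gap: 25-130 chance leads per cancer per analysis if all tested drugs are null, of which it removes about 0.1-10%.

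The sizes rest on assumptions the documents do not supply: 10% exposed, 10% mortality in same-age controls (5-20% for the pooled case), 15-30% in older controls, 500-2,600 drugs tested, and no losses to exclusions or matching. Using five years of pancreas cases, the multiplier behind Table 2's last column, same-age control power would be 38% (d = 1,168) instead of 50%. The conclusion that the rule is not a test of specificity needs none of these figures. It should be changed before the candidate lists are published; it does not invalidate the study.

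**What to change.** 1. **Statistical Analysis, discard rule.** Replace it with the ratio of cancer HR to control HR (drug-by-cohort interaction) and its 95% CI, reported for each control group, and judge specificity on that.
2. **Statistical Analysis and Discussion, multiplicity.** Report Benjamini-Hochberg q-values beside raw P within each cancer and analysis, and make the two sections agree.
3. **Machine Learning.** Say that mined associations are re-examined in the same patients, not confirmed.
4. **Control time origin.** State it: the matched case's diagnosis date, with the control alive on that date.

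All of this is wording and code on existing data. The cost is power. For a drug with HR 0.85 in pancreas cancer and no effect in its same-age matched controls, z = 0.1625 / sqrt(1/675.5 + 1/147.2) = 1.79, so the interaction test has about 43% power. In a simulation of 2,600 drugs with 130 truly cancer specific and 130 general, at the plan's 294 per group, requiring both a 5% Benjamini-Hochberg cut and a significant interaction kept about 26-44 of the 130 specific drugs against about 101 under the present rule. It also cut null drugs kept from about 114 to 2-4, and general drugs kept from 9-61 to about 3. For an exploratory screen I would therefore report q-values and HR ratios with intervals, and not use them as hard cut-offs. A random discovery/replication split is optional, since it costs further power.

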**Methods:**

We plan to monitor a cohort of patients with high-lethality cancers treated in the public health system of Catalonia between 2006 and 2012, retrospectively, for survival for 5 years after diagnosis or until death. A control cohort, comprising people without cancer, will also be retrospectively monitored for 5 years. The following study variables will be extracted from different population databases: type of cancer (patients with cancer cohort), date and cause of death, pharmacological treatment, sex, age, and place of residence. During the first stage of statistical analysis of the patients with cancer cohort, the drugs consumed by the long-term survivors (alive at 5 years) will be compared with those consumed by nonsurvivors. In the second stage, the survival associated with the consumption of each relevant drug will be analyzed. For the analyses, groups will be matched for potentially confounding variables, and multivariate analyses will be performed to adjust for residual confounding variables if necessary. The control cohort will be used to verify whether the associations found are exclusive to patients with cancer or whether they also occur in patients without cancer.

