### Statistical Analysis

To achieve the primary objective, several exploratory analyses will be performed. These will look for an association between the use of the different drugs available in the database (the exposure variable) and patient survival (the outcome variable). The exposure variable will be treated both dichotomously (exposed or not exposed) and quantitatively. The time exposed to the drug, the average monthly dose, the maximum dose, or the cumulative dose per unit of time will be considered. Specific analyses will be carried out on the effect of 2 or more drugs that have been shown to influence survival when they have been consumed, either simultaneously or sequentially, within the time unit being analyzed. The outcome variable is survival during the observation period. Patients who are censored, for whom no death is recorded during the follow-up time, are considered alive at the end of the period.

In addition to the machine-learning techniques described above, the association between exposure and outcome will be investigated using 2 different approaches. The exposure odds for each drug will be calculated, and this exposure will be compared between patients considered alive at 5 years and those who have died using odds ratios (exposure odds ratio). The group of nonsurvivors will be selected with different time criteria in a sensitivity analysis: deceased in the 1st, 2nd, or 3rd year after diagnosis. Second, the survival time of participants exposed and unexposed to each drug available in the database (individual agents, ATC5 codes) or to each family of agents (ATC4 codes) will be compared.

To avoid bias due to a lack of randomization, in both approaches, matching will be carried out between the groups with respect to confounding variables. In addition, if residual confounding is suspected or an imbalance between groups remains after matching, adjustments for age, sex, and diagnostic groups will be performed. A Cox regression model will be constructed to estimate the effect of the evaluated drug. The hazard ratio (HR) and its 95% CI will be reported. Hazard proportionality will be assessed graphically by Schoenfeld residuals.

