
### Sample Size Considerations

Based on a maximum 5-year survival probability of 20% (P=.2, *Q*=.8) and with a significance level of 5% (95% CI) and a power of 80%, it will be possible to detect a difference of 10% between 2 groups with 294 individuals per group. Table 2 shows an initial estimate of the number of survivors at 5 years available during the study period. According to preliminary data not shown, the database available for the study includes a total of 102,860 patients diagnosed with the cancers under study.

**Table 2 table2:** Incidence and estimated survival for the main pathologies under study.

Cancer	New cases each year, n	Estimated 5-year survival, n (%)	Cumulative survivors throughout the study, n
Lung	4079	738 (18.1)	3691
Metastatic colon	6128	852 (13.9)	4259
Metastatic bladder	2444	122 (5)	611
Metastatic kidney	1094	131 (12)	656
Metastatic melanoma	860	171 (19.9)	856
Pancreas	1168	96 (8.2)	479
Esophagus	616	116 (18.8)	579
Metastatic stomach	1089	57 (5.2)	283
Liver	670	118 (17.6)	590

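### Findings reproduced in the control cohort are discarded, but reproduction is not defined and the patient–control difference is never estimated, so the rule can keep shared bias or drop a larger cancer effect

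*Protocol article*

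**What the plan says.** The Methods part of the Abstract gives the purpose of the second cohort: "The control cohort will be used to verify whether the associations found are exclusive to patients with cancer", or whether they occur in people without cancer as well.

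The Statistical Analysis section turns this into a rule. All cancer-cohort analyses are repeated in a same-age control group and in a group 10 years older, and "The findings that are reproduced in these groups of the control cohort will be discarded". The reason given is that such findings reflect uncontrolled bias or general survival effects. The article does not say what direction or size counts as reproduction, or whether one control group is enough.

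The next paragraph holds the only criterion for a result: "To consider a result statistically significant, the P value will be set at P=.05". It adds that "no correction techniques will be applied to the P values obtained". For the Cox models, "The hazard ratio (HR) and its 95% CI will be reported". No drug-by-cohort interaction or ratio of HRs is mentioned.

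**The concern.** Exclusivity to cancer is a statement about a difference between two effects. A significant result in one cohort and a non-significant one in another does not show that the effects differ, and two significant results do not show that they are equal.

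The cohorts also carry very different information. At least 80% of patients are expected to die within 5 years. The article expects lower mortality in the same-age controls, gives no figure for either control group, and has no power calculation for controls.

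Two errors follow if separate tests decide:

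- Bias common to both cohorts survives as an apparently cancer-specific drug effect when the controls have too few deaths to show it.
- A drug with a large effect in cancer is removed because the controls, being numerous, reveal a small one. It then never reaches the confirmatory studies on which the protocol relies.

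**Working it through.** **The plan's own figure.** Sample Size Considerations starts from "Based on a maximum 5-year survival probability of 20"%, "with a significance level of 5% (95% CI) and a power of 80"%, and reaches 294 per group for a 10-point difference. For 20% versus 30%, two-sided, pooled variance:

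n = [1.96·√(2·0.25·0.75) + 0.84·√(0.2·0.8 + 0.3·0.7)]² / 0.1² = 293.2, rounded up to 294. It reproduces. The effect corresponds to HR = ln 0.30 / ln 0.20 = 0.75.

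**The planned effect carried into the controls.** Suppose the same HR of 0.75 is pure bias in both cohorts. With two controls per patient in each control group there are 588 per exposure group. Power at P=.05 is 31% if control survival is 90%, and 55% if it is 80%. The bias then escapes with probability (1 − 0.31)(1 − 0.55) = 31% if either group can discard it, and 1 − 0.31·0.55 = 83% if both must.

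**Larger groups: inputs**

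- From Table 2: pancreas 1,168 cases a year, 8.2% survival; lung 4,079 a year, 18.1% survival.
- From Duration: 2006 to 2012 inclusive, so 7 years. Pancreas 1,168 × 7 = 8,176; lung 4,079 × 7 = 28,553.
- From Sample Size Considerations: whole cohort 102,860.
- From Participants and Settings: two same-age and two older controls per patient, so each control group is twice the patient group.
- Assumed, not in the article: 5% drug use; 5-year mortality 10% (range 5–15%) in same-age controls and 30% (20–40%) in older controls; shared bias HR 0.85.
- Inferred: reproduction means two-sided P<.05 in the same direction.

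**Formulas.** SE(log HR) = 1/√(deaths × 0.05 × 0.95); power = Φ(|log HR|/SE − 1.96).

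**Error 1, shared bias, pancreas-sized group**

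| Cohort | Deaths | SE | Power for HR 0.85 |
|---|---|---|---|
| Patients | 8,176 × 0.918 = 7,506 | 0.053 | 87% |
| Same-age controls | 16,352 × 0.10 = 1,635 | 0.113 | 30% |
| Older controls | 16,352 × 0.30 = 4,906 | 0.066 | 70% |

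Passes if one reproduction discards: (1 − 0.299)(1 − 0.699) = 21%. Passes if both are needed: 1 − 0.299·0.699 = 79%. The same calculation for other sizes:

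| Group | One reproduction discards | Both needed |
|---|---|---|
| Pancreas-sized | 21% (11–39%) | 79% (66–91%) |
| Lung-sized | 0.1% (0–1.8%) | 24% (9–54%) |
| Whole cohort | about 0% | 0.1% (0–5%) |

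**Error 2, large groups.** Each whole-cohort control group has 2 × 102,860 = 205,720 people. At 10% mortality that is 20,572 deaths, and SE = 0.032. For HR 0.90, |log HR| = 0.105, so power = Φ(3.29 − 1.96) = 91%. A drug with an HR of, say, 0.50 in cancer would usually be discarded because of it.

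**Error 2, pancreas-sized group.** With cancer HR 0.60 and control HR 0.85, the drug is discarded 1 − 0.21 = 79% (61–89%) of the time if one reproduction suffices, and 21% (9–34%) if both are needed.

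**A direct comparison in that last scenario.** Pooling the control groups gives 1,635 + 4,906 = 6,541 deaths. SE of the log ratio = √[(1/7,506 + 1/6,541)/(0.05 × 0.95)] = 0.078. The ratio of HRs is 0.60/0.85 = 0.71, expected 95% CI about 0.61 to 0.82, with power 99.4% (97.4–99.8%). Under shared bias the expected ratio is 1.00, with an interval of about 0.86 to 1.16.

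**The case against.** Several stronger readings are tempting, and the article does not support them.

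- *The protocol fixes P=.05 as the test of reproduction.* It does not say so. The significance criterion stands in a separate paragraph, and HRs with intervals are also reported, so size and direction could be used. The article also leaves details to the substudy papers. What stands is that an irreversible keep-or-discard rule is fixed while its key word is undefined, and that no stated analysis estimates the difference.
- *The control check is the only protection against bias.* It is not. Statistical Analysis plans matching and adjustment. Methods to Address Potential Sources of Bias removes drugs prescribed shortly before death, restricts exposure to a time window among those still alive, and excludes patients under closer surveillance. The control check adds to these. The Discussion does concede that some reverse-causality and immortal-time effects may remain.
- *The controls have too few deaths in general.* The 4:1 ratio and the older subcohort were chosen with mortality in mind and reduce this problem. It is confined mainly to less-used drugs and smaller cancer groups.
- *The rule contradicts the primary objective.* Removing general survival effects is a declared screening choice. The objection that survives is narrower: the rule also removes drugs whose cancer effect clearly exceeds the general one.
- *Five-year odds ratios are misleading across cohorts.* Nothing in the article compares their size between cohorts, so this adds nothing here.

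The exploratory label is a fair argument on severity. It does not make the rule sound, because discarded candidates are not carried forward for confirmation.

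**Conclusion.** The concern holds in limited form. The discard rule does not measure cancer specificity, and its key term is undefined. If P=.05 is the criterion, both errors occur, and which one dominates depends on group size and drug use. Shared bias passes appreciably in a pancreas-sized group (21% or 79%, depending on how many control groups must reproduce it). In a lung-sized group it passes only if both must reproduce it (24%, against 0.1%), and in the whole cohort hardly at all. Wrongful discarding grows as the controls become more informative.

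These percentages rest on assumed drug use, control mortality and bias size, and on an inferred criterion; they illustrate the problem and do not predict its frequency. The logical point does not depend on them. Severity: should be fixed.

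**What to change.** In Statistical Analysis, replace the discard rule as follows.

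- For each drug, fit patients and controls in one Cox model with a drug-by-cohort term. Report the cancer HR, the control HR and the ratio of HRs, each with a 95% CI.
- Call a drug a cancer-specific candidate only if the cancer HR itself meets the significance criterion and the ratio's interval excludes 1, with the cancer effect the stronger one in the same direction, or with no effect in controls.
- Label the other drugs *general effect or shared bias* or *specificity not shown*, give both HRs, and do not delete them.
- State that a ratio different from 1 does not rule out bias that differs between the cohorts.

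The condition on the cancer HR is needed. With cancer HR 1.00 and control HR 0.85 the ratio is 1.18, and in the pancreas-sized scenario its interval would exclude 1 about 55% of the time, although the drug does nothing in cancer.

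The cost is a change of wording and one model term, with no new data. The ratio has a wider interval than a single HR, so fewer drugs will be called cancer-specific. The Results section says that analyses have begun, so the change should be made before findings are filtered.
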